## Methods/design

### Design

To evaluate the effectiveness of an intervention recently developed for PLH in Botswana, an RCT will be performed. The trial will have two conditions: an intervention group, who will receive the self-help program with coaching for depressive symptoms, and an attention-only control group, who will receive the self-help program without coaching following completion of the follow-up measurement. Random allocation of participants to the intervention or control group will be performed using a stratified random sampling technique. The sample will be stratified according to gender and treatment center. It is important to stratify by gender to ensure approximately equal proportions of males and females in the intervention and control groups. In the study by [name] et al. that investigated intervention targets for depressive symptoms among PLH in Botswana, more females participated compared to males. Additionally, treatment centers are expected to differ with regard to the number of patients included; therefore, stratification will ensure that both the intervention and control groups in large and small treatment centers have almost the same numbers of patients in both conditions.

Random number tables will be used to allocate participants to either condition; these will be computer generated and produced by an independent researcher. Randomization will be done in permuted blocks of six. The independent researcher will enter the numbers into an Excel file which will conceal the randomization until after the participants are established in the trial. The randomization is set up such that the main researcher is unable to see treatment allocation beforehand, minimizing bias. Participants and coaches will not be blinded to allocation to conditions. Participant allocation to one of the conditions will be done after the pre-test.

The study is approved by the Health Research Development Committee of the Ministry of Health in Botswana (Ref. HPDME 13/18/1). The Standard Protocol Items: Recommendations for Interventional Trials (SPIRIT) checklist is provided as Additional file 1.

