### Ethical precautions

Coaches will monitor the depressive symptoms of all participants on a weekly basis by asking how the participants are doing. When participants express severe depressive symptoms, the PHQ-9 will be administered. In case of any participant in either condition showing severe depressive symptoms (PHQ-9 > 20) or suicide ideation, the coaches will follow referral guidelines. The coaches will discuss the situation with the participant before any steps are taken. The coaches will also discuss all steps with the psychologist. The participant can be referred to a medical doctor, his/her general practitioner, or the HIV treatment center. A participant who is referred for intensive treatment to a psychologist or psychiatrist may continue with the study. However, in the analysis, the referral will be entered as a covariate to account for the influence of the treatment. These guidelines are contained in the study protocol for coaches.

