To measure depressive symptom severity (primary outcome), we will use the PHQ-9 [26] and the Center for Epidemiological Studies Depression Scale (CES-D) [29]. Secondary outcomes include physical tension (physical tension questionnaire), activation (Behavioral Activation for Depression Scale (BADS) [30]), cognitive coping (Cognitive Emotion Regulation Questionnaire-short (CERQ-short) [31]), behavioral coping (Behavioral Emotion Regulation Questionnaire (BERQ) [32]), symptoms of anxiety (Generalized Anxiety Disorder 7 (GAD-7) [33]), negative life events (Life Events Scale [34]), self-efficacy ([name] and [name], “Self-efficacy questionnaire,” unpublished), goal reengagement [35], social support, alcohol and substance abuse [36], and demographic variables. Some of the measures are single-item questions that are based on the original scales. The items were selected based on item-total correlations from our earlier research that investigated prevalence and risk factors of depressive symptoms of PLH in Botswana ([name] et al., “Depressive symptoms among people living with HIV/AIDS in Botswana: a search for intervention targets for a coping-skills intervention,” submitted). We will also measure the participants’ motivation to start the intervention, compliance, dropout and reasons for the dropout, and user satisfaction.

Through a self-designed questionnaire, we will collect information on demographic characteristics (such as age, gender, and level of education) and clinical and psychological characteristics (such as age, depressive symptoms severity, physical health, HIV status, alcohol and substance use, motivation, and social support) as potential moderators of treatment. We will measure treatment mediators and depressive symptoms (dependent variable) during the intervention as well as during the waiting period for the control condition. The following mediator variables will be assessed in the study: physical tension (one item), activation (one item), coping (four subscales from the CERQ-short: rumination, catastrophizing, positive refocusing, and refocus on planning), self-efficacy (one item), and goal reengagement (six items). This makes it possible to examine which mechanisms precede change in the primary outcome.

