### Statistical analyses

Data will be analyzed using an intention-to-treat (ITT) analysis [43]. We will use a two-tailed alpha of 0.5 for significance testing. To investigate baseline differences between conditions, we will use chi-square and analysis of variance (ANOVA) tests for categorical and continuous variables, respectively.

Differences between groups in depressive symptoms from pre-test to post-tests will be investigated using longitudinal multilevel regression analyses (LMRAs) [44]. We will adopt a two-level model where time and group will be included as fixed effects and the slopes for time and the intercept as random effects. The between-group analysis will include the pre-test, post-test, and follow-up. To investigate the long-term effects of the intervention, we will include the pre-test, post-test, and follow-up in the within-group analysis. To estimate the effects in the model, we will employ a maximum likelihood estimation type. We will also study the differences between participants who followed the intervention to the end and those who dropped out with chi-square tests and ANOVAs.

Furthermore, Cohen’s *d* will be used to calculate within- and between-group effect sizes. Effect sizes less than 0.20 are regarded as having a small effect, 0.50 a medium effect, and 0.80 a large effect [45]. We will also explore clinically significant differences for individual change in depressive symptoms. Individual change scores of 5 or more for the PHQ-9, from pre-test to post-test and follow-up, will be regarded as clinically significant [46]. The same approach will be used to examine pre-treatment versus post-treatment changes with regard to all secondary outcomes.

We will examine moderators of the treatment outcome using LMRA. We will enter potential moderators individually. Additionally, we will employ the latent difference score model for mediation analysis [47].

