The present study also has limitations. Firstly, it is a booklet self-help program; thus, only those who can read and write can use the program. This could hamper the generalizability of our results. Secondly, we will exclude all participants whose depressive symptoms scores place them in the severely depressed range or those who indicate that they are suicidal. While these patients could still benefit from the self-help program, they require more intensive treatment. Additionally, we will conduct the follow-up 3 months following the post-test. While this period might be considered short, our argument is that it would not be ethical for participants in the control group to wait as long as 8 months before they can start the intervention. We will therefore enroll the control group to start the intervention after the 3 months follow-up.

Another limitation of the study is that, in resource-limited settings, the aspect of coaching required by this program might become an obstacle in implementing the program. Therefore, it would be necessary for future research to explore the effectiveness of the program without coaching. Furthermore, for ethical reasons, we could not include a condition without coaching to study whether coaching could influence the outcome. This is also a question that can be addressed by future research. Lastly, participants will be screened using a short screening tool (PHQ-9) for depressive symptoms, and some may argue that this tool alone is not sufficient to make a diagnosis of depression. However, the current study aims to only assess and treat depressive symptoms and not to make a diagnosis for a depressive disorder. In addition, the PHQ-9 is validated as a reliable measure for depressive symptoms severity [26, 38]. Furthermore, the presence of mild to moderate depressive symptoms is part of the inclusion criteria and not a diagnosis of a depressive disorder.

In conclusion, we aim to investigate the effectiveness of a booklet self-help with coaching intervention program for depressive symptoms among PLH. The program runs for 6 weeks (maximum 8 weeks) and includes six lessons. If the program is found to be effective, it may be implemented in Botswana. In addition, the program may be adapted and implemented in other sub-Saharan countries.

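### Referral after randomisation is to be entered as a covariate with no limit to a sensitivity analysis, which can move the group effect away from the declared intention-to-treat effect

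*Protocol article*

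**What the plan says.** Three parts of the Protocol article bear on this.

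- **Ethical precautions.** Coaches check on every participant weekly: "Coaches will monitor the depressive symptoms of all participants on a weekly basis by asking how the participants are doing". The trigger applies to both arms: "In case of any participant in either condition showing severe depressive symptoms (PHQ-9 > 20) or suicide ideation, the coaches will follow referral guidelines". Those referred stay in: "A participant who is referred for intensive treatment to a psychologist or psychiatrist may continue with the study". Then comes the analysis rule: "in the analysis, the referral will be entered as a covariate to account for the influence of the treatment".
- **Design and Assessments.** On timing, "Participant allocation to one of the conditions will be done after the pre-test". On the outcome, "To measure depressive symptom severity (primary outcome), we will use the PHQ-9 [26] and the Center for Epidemiological Studies Depression Scale (CES-D) [29". The PHQ-9 is therefore both a primary outcome scale and a referral trigger.
- **Statistical analyses.** "Data will be analyzed using an intention-to-treat (ITT) analysis". The model is a two-level longitudinal regression on pre-test, post-test and follow-up, with time and group fixed and random intercepts and time slopes. Referral is not mentioned there.

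**The concern.** A covariate in a randomised comparison is safe when treatment cannot have influenced it. Referral fails that test. It is decided during the programme, after allocation, on the basis of severity on a scale that is also the outcome. Severe and suicidal cases are kept out at entry ("we will exclude all participants whose depressive symptoms scores place them in the severely depressed range or those who indicate that they are suicidal"), so most referrals reflect a state that arose or came to light later.

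This has three consequences:

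1. If the programme works, fewer intervention participants are referred. Holding referral fixed then removes part of the effect under test.
2. Coaches are unblinded, and calls last about 15 minutes in the intervention arm against about 5 in the control arm. Detection of severe symptoms may therefore differ by arm, which can shift the group coefficient even with no true effect.
3. The stated purpose, allowing for outside treatment, is not met. Referred people are sicker, so the covariate mixes their severity with any benefit of the care they receive.

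At stake is whether the reported group effect is the intention-to-treat effect the plan promises.

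**Working it through.** **The plan's own figure.** A two-sample t-test with d = 0.50, two-sided alpha 0.05 and power 0.80 needs 63.8, so 64 per group, as stated. Dropout of 15%: 64/0.85 = 75.3, against the stated 75. Neither is in dispute.

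**Size of the shift.** The documents give no referral rate and no correlation between on-study and later severity. Everything below is therefore assumption, on a standardised outcome with 2,000,000 simulated participants:

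- baseline y0 ~ N(0,1); arm g = 0 or 1
- M0 = √0.6·y0 + e, var(e) = 0.4; on-study severity M = M0 − 0.4g
- referred r = 1 if M exceeds a cut
- post-test y1 = 0.8·M0 − 0.5g + γr + N(0, 0.6²), where γ is the effect of outside care

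Four fits with γ = 0 (true effect 0.50 SD; without referral every model returns 0.50):

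| Referred, control / intervention | ANCOVA (y1 on g, y0, r) | Group × time, r time-invariant | Group × time, r time-varying, pooled | Group × time, r time-varying, random intercept |
|---|---|---|---|---|
| 2.2% / 0.8% | 0.49 | 0.50 | 0.47 | 0.49 |
| 3.6% / 1.4% | 0.48 | 0.50 | 0.46 | 0.48 |
| 6.7% / 2.9% | 0.47 | 0.50 | 0.43 | 0.47 |
| 11.5% / 5.5% | 0.45 | 0.50 | 0.40 | 0.46 |

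The group × time fits stack pre-test and post-test, with r set to 0 at pre-test when time-varying. Follow-up and random slopes were not simulated. The pooled fit ignores within-person correlation; the random-intercept fit is nearer to the plan's model.

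**Does the covariate isolate outside treatment?** Set γ = −0.3, so referral care truly lowers scores. In the last row the intention-to-treat effect is then 0.48, and the effect had nobody received outside care is 0.50. The adjusted ANCOVA gives 0.45, which is neither. The referral coefficient is +0.48, opposite in sign to the true −0.3.

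**No true effect.** A second simulation on the PHQ-9 scale assumed SD 5, baseline restricted to the eligible range, and correlation 0.7 between on-study and post-test residuals.

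- Equal detection: the adjusted group effect is zero to within simulation error.
- Control-arm detection half that of the intervention arm (2.8% to 17.8% referred in the latter): a spurious benefit of 0.10 to 0.44 points, or 0.02 to 0.09 SD (divide by 5).
- Detection reversed: a spurious harm of 0.09 to 0.44 points.

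**Power.** An unadjusted t-test at d = 0.45 gives:

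- 71% at 64 per arm
- 83% at 85 per arm (200/2 = 100; 100 × 0.85 = 85)
- 89% at 100 per arm

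**The case against.** **The size may be nil.** Under a plain reading of entering a covariate, referral is a time-invariant main effect, and the group-by-time contrast does not move. This stands. The article does not state the coding, so a shift is possible, not certain.

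**Referral may be rare.** Severe and suicidal cases are excluded at entry, the severity trigger is high, and the rule concerns referral to a psychologist or psychiatrist in a country the Background describes as having about 10 psychiatrists. This is a fair point: near 2% referred in the control arm, the ANCOVA shift is about 0.01 SD. Suicide ideation is also a trigger, however, and no rate is given.

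**The rule may not reach the primary model.** Statistical analyses lists only time and group as fixed effects, and an unseen SAP may settle the matter. But the rule as written is general, and the two sections disagree on their face. That is a stated rule to correct, not an omitted detail.

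**Stronger readings that do not hold.**

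- A reader might infer that power falls from 80% to 71%. That applies an unadjusted t-test at 64 per arm. The trial recruits 200, and the 85 and 100 per arm figures stay above 80%. Adjusting for baseline also shrinks the residual SD (0.785 without referral and 0.760 with it, in the last row of the table), so the 71% does not describe the ANCOVA either.
- A reader might infer that referral follows from the primary endpoint itself. It follows from earlier severity on the same scale, not from the post-test or follow-up score.
- A reader might infer that false positives are likely. They require detection to differ by arm, which the call lengths and lack of blinding make plausible but do not establish.

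**Conclusion.** The rule is unsound for a primary intention-to-treat analysis and conflicts with Statistical analyses. Conditioning on referral makes the group coefficient a comparison at fixed referral status, and it answers neither the intention-to-treat question nor the question of what would happen without outside treatment.

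The size cannot be fixed from the documents. Over the assumed range the loss runs from nothing to 0.05 SD in most fits, and to 0.10 SD in the pooled time-varying fit. The direction is towards zero if the programme prevents referrals, and either way if detection differs. These figures rest on the assumed severity correlations, on most of the effect being present when referral is decided, and on the coding of referral. The defect is firm and its magnitude is uncertain.

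**What to change.** Reconcile Ethical precautions with Statistical analyses:

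1. State that the primary model contains no covariate measured after randomisation, and remove referral from it.
2. Analyse all randomised participants as allocated, using their scores whether or not they were referred (treatment-policy handling).
3. Report the number referred, by arm.
4. Confine any referral-related analysis to a labelled sensitivity analysis that names the effect it targets, for example setting scores after referral to missing and using multiple imputation.

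The cost is a sentence or two in the protocol or SAP. Referral procedures and data collection stay as they are. Trial status says recruitment had not begun, so the change can be made before any outcome is seen.

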### Assessments

The data will be collected at six different times during the trial (T0, three in-between assessments during the intervention, T1, and T2). Table 1 shows each stage of the study and the assessments that will be used. The initial screening (PHQ-2) will be done at the treatment centers by HIV nursing staff and doctors. At T0, T1, and T2, the researchers will conduct the assessments via a standardized telephone interview. The three in-between assessments will be conducted by the coaches by telephone.

**Table 1 Tab1:** Summary of assessments for the study

Assessment	Screening HIV treatment centers *(+/− 5 min)*	Screening researchers *(+/− 10 min)*	T0: pre-test *(+/− 25 min)*	Three times during intervention/waiting period^1^ *(+/− 10 min)*	T1: post-intervention/waiting period: 6–8 weeks after T0^1^ *(+/− 20 min)*	T2: 3 months follow-up *(+/− 20 min)*
PHQ-2	X	–	–	–	–	–
PHQ-9	–	X	X	–	X	X
CES-D	–	–	X	–	X	X
Demographics and other information	–	–	X	–	X	X
Physical tension questionnaire	–	–	X	X	X	X
BADS	–	–	X	X	X	X
CERQ-short	–	–	X	X	X	X
Self-efficacy questionnaire	–	–	X	X	X	X
Goal Disengagement and Reengagement Scale	–	–	X	X	X	X
BERQ	–	–	X	–	X	X
GAD-7	–	–	X	–	X	X
PHQ-4	–	–	–	X	–	–
Life Events Scale	–	–	X	–	X	X
Motivation	–	–	X	–	–	–
Social support	–	–	X	–	X	X
Alcohol and substances	–	–	X	–	X	X
Compliance	–	–	–	X	X	–
Dropout	–	–	–	X	X	–
User satisfaction questionnaire	–	–	–	–	X	–

*PHQ-2* Patient Health Questionnaire 2, *PHQ-9* Patient Health Questionnaire 9, *CES-D* Center for Epidemiological Studies Depression Scale; BADS = Behavioral Activation for Depression Scale, *CERQ* Cognitive Emotion Regulation Questionnaire, *BERQ* Behavioral Emotion Regulation Questionnaire, *GAD-7* Generalized Anxiety Disorder 7, *PHQ-4* Patient Health Questionnaire 4

^1^Not asked to participants in the control group

To measure depressive symptom severity (primary outcome), we will use the PHQ-9 [26] and the Center for Epidemiological Studies Depression Scale (CES-D) [29]. Secondary outcomes include physical tension (physical tension questionnaire), activation (Behavioral Activation for Depression Scale (BADS) [30]), cognitive coping (Cognitive Emotion Regulation Questionnaire-short (CERQ-short) [31]), behavioral coping (Behavioral Emotion Regulation Questionnaire (BERQ) [32]), symptoms of anxiety (Generalized Anxiety Disorder 7 (GAD-7) [33]), negative life events (Life Events Scale [34]), self-efficacy ([name] and [name], “Self-efficacy questionnaire,” unpublished), goal reengagement [35], social support, alcohol and substance abuse [36], and demographic variables. Some of the measures are single-item questions that are based on the original scales. The items were selected based on item-total correlations from our earlier research that investigated prevalence and risk factors of depressive symptoms of PLH in Botswana ([name] et al., “Depressive symptoms among people living with HIV/AIDS in Botswana: a search for intervention targets for a coping-skills intervention,” submitted). We will also measure the participants’ motivation to start the intervention, compliance, dropout and reasons for the dropout, and user satisfaction.

Through a self-designed questionnaire, we will collect information on demographic characteristics (such as age, gender, and level of education) and clinical and psychological characteristics (such as age, depressive symptoms severity, physical health, HIV status, alcohol and substance use, motivation, and social support) as potential moderators of treatment. We will measure treatment mediators and depressive symptoms (dependent variable) during the intervention as well as during the waiting period for the control condition. The following mediator variables will be assessed in the study: physical tension (one item), activation (one item), coping (four subscales from the CERQ-short: rumination, catastrophizing, positive refocusing, and refocus on planning), self-efficacy (one item), and goal reengagement (six items). This makes it possible to examine which mechanisms precede change in the primary outcome.

On the basis of findings from our previously mentioned study that investigated the prevalence and risk factors of depressive symptoms, needs of PLH, and feasibility of an intervention program in a sample of 291 PLH in Botswana, we decided to use shortened questionnaires where possible, because respondents had great difficulty completing all the questionnaires. Where available, we used existing short versions, such as the CERQ-short, PHQ-2, and PHQ-4. Regarding the rest of the shortened questionnaires, the best items were selected based on item-total correlations in the data from the baseline study to ensure that they best fit our sample.

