**Methods/design:**

A randomized controlled trial will be conducted to compare the booklet self-help program with coaching with an attention-only control condition, by including pre-test, post-test, and follow-up assessments. We aim to enroll 200 participants with mild to moderate depressive symptoms into the study. The self-help program contains the following main components: activation, relaxation, changing maladaptive cognitions, and the attainment of new personal goals. This content is covered over six lessons to be completed in a maximum of 8 weeks. It uses a combination of psycho-education, assignments, and exercises. The participants will work on the program 1–2 h every week for 6 weeks (maximum 8 weeks). Coaches will offer support and motivate the participants. For both groups, depressive symptoms and possible mediators will be measured three times during the intervention, and at pre-test, post-test, and follow-up.

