**Fig. 1 Fig1:**
[figure not shown]
Flowchart of the study design

In Botswana, the majority of patients who have been on treatment for more than a year visit the treatment center once every 6 months; therefore, the screening will be conducted over a period of approximately 6 months. Any patient who obtains a score > 0 on the PHQ-2 and who meets the inclusion criteria may be referred to the researchers. The HIV consultants will provide written information about the study to the patients and request for permission to provide the researchers with the patient’s contact information (telephone number or email). Following contact with the patients, the researchers will provide further information to the patients and conduct extensive screening for depressive symptoms using the PHQ-9 by telephone. Patients with a score within the mild (> 4) and moderate (< 20) ranges will be eligible for participation in the trial. These patients will then be invited to participate. Those who agree to participate will give consent by a text message to the researchers. Additionally, we will seek permission from patients to inform a medical doctor or general practitioner at the HIV treatment center about their participation in the study. Participants will then undergo a pre-test (T0). Thereafter, the participants will be randomly assigned to the intervention or the control (attention-only) group. The coaches will call all participants at the beginning of the intervention to assess for and stimulate their motivation. This will be accomplished through the use of motivational interviewing and general conversational techniques, providing information about the program, helping the patients plan for the lessons, and advising them to engage in a small activity to get started.

The intervention group will then receive the self-help treatment program with coaching by telephone, while the control group will only receive attention through a weekly telephone chat from a coach. The participants will work on the intervention for 6 weeks (with a maximum extension of 2 weeks). During the intervention, participants will be asked to answer standardized questions at three different times. At 8 weeks, all participants will complete the post-test (T1) and subsequently the follow-up measurement (T2) 3 months later. After the follow-up, participants in the control condition will receive the intervention.

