The pre-test, post-test, and follow-up assessments will be done by the researchers through a standardized telephone interview; the three assessments during the intervention will be done during the coaching sessions, after the completion of lessons 1 (activation), 2 (physical relaxation), and 4 (changing negative thinking patterns). Callers will follow a standard script where they will explain who they are and the purpose of the interview. Participants will be asked questions exactly as they appear on the questionnaire. The answer categories for each section will be called out, and the participants will be asked to write them down for easy reference. Callers are allowed to repeat questions at the request of the participant.

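### Table 1's footnote excludes controls from the T1 and in-between assessments, against the text, and the in-between assessments are triggered by lessons that controls receive only after T2

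*Protocol article*

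**What the plan says.** **Table 1 (Assessments).** Two column headings carry marker 1: "Three times during intervention/waiting period^1" and "T1: post-intervention/waiting period: 6–8 weeks after T0^1". The note to that marker reads "Not asked to participants in the control group". The follow-up heading, "T2: 3 months follow-up", has no marker, and neither does T0.

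**Text on who is assessed.** The abstract (Methods/design) states: "For both groups, depressive symptoms and possible mediators will be measured three times during the intervention, and at pre-test, post-test, and follow-up". The Procedure section states: "At 8 weeks, all participants will complete the post-test (T1". The Assessments section has mediators and depressive symptoms measured in the controls' waiting period. The PHQ-4 section gives that scale to controls during the same period. The user satisfaction section gives controls 11 questions about their coach, and Table 1 schedules that questionnaire at T1 only.

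**Timing.** The Procedure section places the in-between assessments in coaching sessions "after the completion of lessons 1 (activation), 2 (physical relaxation), and 4 (changing negative thinking patterns". Controls receive the programme only after T2 (Design; Procedure). T1 falls at 8 weeks in the Procedure section, but the Table 1 heading reads "T1: post-intervention/waiting period: 6–8 weeks after T0".

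**The concern.** A marker on a column heading governs every row in that column. The T1 column includes PHQ-9, CES-D and the secondary outcomes. The in-between column includes PHQ-4 and all the mediators. Read as printed, the table tells staff not to ask controls any of these.

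The Statistical analyses section puts pre-test, post-test and follow-up into the between-group model and plans a latent difference score model for mediation. The Assessments section justifies the in-between waves as the way to see which mechanisms come before change in the outcome. Both uses need control data at the marked time points, and a post-test that was not taken cannot be collected later.

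The lesson trigger is a second gap, and it would remain if the footnote were corrected. Controls have no lessons in the comparison period, so the rule gives no date for their in-between assessments. In the intervention arm it makes the existence and timing of each wave depend on progress through the booklet. Coaching stops at 8 weeks even if lessons are unfinished (Support from a coach). A participant who has not completed lesson 4 by then therefore has neither a trigger nor a session for the third wave.

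**Working it through.** This is mainly a consistency check. The only stated figures that bear on it are those for sample size.

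**1. The plan's own figures (Sample size).** Inputs: effect size 0.50, two-sided alpha 0.05, power 0.80, dropout 15%, 200 recruited.
- Two-sample t-test: n = 63.77, rounded up to 64 per group, as stated. The normal approximation gives 63.
- Dropout: 64 / (1 − 0.15) = 75.3, rounded up to 76. The stated 75 agrees within rounding.
- No stated number is wrong on this point.

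**2. Side-by-side reading for controls.**

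| Time point | Table 1, read literally | Text |
|---|---|---|
| T0 | assessed | assessed |
| Three in-between | not asked | both groups (abstract); waiting period (Assessments; PHQ-4) |
| T1 | not asked | all participants (Procedure); both groups (abstract); 11 satisfaction questions |
| T2 | assessed | all participants |

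The two marked headings also contain the term waiting period, which can only refer to controls. The table therefore disagrees with itself as well as with the text.

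**3. What the literal reading would cost.** With 1:1 allocation (an assumption, since the ratio is not stated), 200 / 2 = 100 controls.
- Control observations: 0 of 100 at T1 and 0 of 100 at each in-between wave.
- T1 contrast: not estimable from observed data. If time were coded as a straight line, the model would still return a T1 difference, but the control value would be an interpolation between T0 and T2.
- T2 contrast: survives. Power at effect size 0.50 is 90.0% with 15% dropout (85 per arm), 86.0% with 25% (75 per arm) and 80.1% with 36% (64 per arm).
- Mediation: controls keep mediators at T0 and T2. They lose the waves that would show the order of change.

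**4. If T1 is collected in both arms, as the text says.** Power at T1 is 80.1% with 64 completers per arm and 86.0% with 75. The planned comparison is intact.

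**5. Lesson trigger.** Take an even pace as an illustration. Six lessons in 6 weeks put the end of lesson 4 at 4 × 6/6 = 4.0 weeks. Six lessons in 8 weeks put it at 4 × 8/6 = 5.3 weeks. Among completers the third wave can thus move by about 1.3 weeks. Participants who do not complete lesson 4 have no third wave, and controls have no stated date.

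**6. T1 rule.** The two statements differ by up to 8 − 6 = 2 weeks. T2 is set 3 months after T1, so the ambiguity carries over to T2.

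**The case against.** A reader might infer that the trial has no control arm for its primary or mediation comparison. The document does not support that. T2 is unmarked, controls keep outcomes and mediators at T0 and T2, and the between-group model includes follow-up. No single primary time point is named.

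A reader might also infer that the investigators mean to leave controls unmeasured at T1. The text points the other way in at least five places. The Compliance row is marked in exactly the two footnoted columns, which fits a note meant for programme-only items. That explanation is an inference, and the article does not state it.

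Nor can it be said that interviewers work from Table 1. Its title calls it a summary, and callers and coaches follow scripts that are not shown. Losing all control T1 data would require staff to follow one footnote against the rest of the text, so it is a worst case and not a forecast. It would also be wrong to say that controls never receive the lessons, because they receive them after T2.

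On the trigger, the choice of control calls is the kind of detail a coach manual may hold. Measuring after particular lessons also has a rationale, because it lines up each mediator with the content meant to change it. Moving to fixed weeks in both arms would weaken that link and is a trade-off.

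All of this stands and limits the claim. It does not remove the contradiction, which is explicit in the current text and not an omission. It also does not supply a rule that could apply to controls, since the only trigger stated is one they cannot meet before T2.

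**Conclusion.** The point holds as an internal contradiction that should be corrected before recruitment. The footnote is wrong as attached. Followed literally, it would remove all control PHQ-9, CES-D and secondary outcome data at T1 (0 of about 100, assuming 1:1 allocation) and all control mediator and PHQ-4 data at the three in-between points. The post-test contrast and the test of temporal order in the mediation analysis would go. A T0-to-T2 contrast would remain, with roughly 80% to 90% power for dropout between 36% and 15%. If staff follow the text, nothing is lost at T1.

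The lesson trigger is a separate and smaller gap. The in-between waves have no stated timing in controls, and in the intervention arm they depend on adherence. The documents give no basis for sizing the resulting missing data. The difference in T1 wording is minor, but one rule is needed.

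**What to change.** 1. Remove marker 1 from both column headings in Table 1. Attach it only to the Compliance row and to the programme part of the satisfaction questionnaire. Controls keep their 11 coach questions.
2. State which of the controls' six calls carry the three in-between assessments, matched in time to the intervention arm. If each coaching session follows the lesson of the same number, calls 1, 2 and 4 are the natural counterparts. The investigators should confirm this.
3. In the intervention arm, collect each in-between assessment at its matched time even if the lesson is unfinished. Record the lesson reached, which the compliance questions already ask.
4. Reconcile the two T1 statements into one rule for both arms, and count T2 from it.

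**Cost.** A table correction and a few lines in the caller and coach scripts. Controls are already called six times over 6 to 8 weeks, so no contacts are added, although three of their roughly 5-minute calls would have to carry an assessment that Table 1 puts at about 10 minutes. The downside is small: some intervention participants will be assessed before finishing a given lesson, which loosens the alignment between lesson and mediator. The Trial status section says recruitment has not begun and materials are still being translated, so the change can be made before any data are affected.
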